## Methods/design

### Trial design

D-CPT is an open, rater-blinded, multicenter, 2-arms RCT comparing D-CPT to TAU in Germany. There are five assessments: at baseline, within the treatment (approx. 8 weeks after beginning), directly after end of treatment (post-treatment) as well as 3 and 6 months after end of treatment (follow-up 1 and 2).

### Study centers

The D-CPT project is designed as a multicenter study with [name] (University Eichstätt-Ingolstadt) as principal investigator. Treatment is offered in three university outpatient clinics: Freie Universität Berlin (supervised by [name]), Goethe University Frankfurt am Main (supervised by [name]), and University Eichstätt-Ingolstadt (supervised by [name]). Moreover, there are four partner projects at different research sites. Besides being a clinical center, the work group at Goethe University Frankfurt am Main ([name]) studies potential predictors of treatment outcome. The analysis of epigenetic profiles of PTSD patients by saliva samples during the course of therapy is the task of a research group from the Max-Planck Institute of Psychiatry in Munich ([name]). At the University Medical Center Hamburg-Eppendorf ([name]), direct and indirect costs of the disorder are evaluated. Bielefeld University ([name]) examines the neurophysiological processing of threat cues in PTSD and their respective changes in the course of the treatments. The D-CPT network and its study centers are displayed in Figure 1.

**Figure 1 F1:**
[figure not shown]
**The D-CPT network and its study centers.** RCT, Randomized controlled trial; PI, Principal investigator.

### Participants

Adolescents and young adults aged 14 to 21 years may take part in the study. For inclusion, PTSD as a primary diagnosis after experiencing CSA and/or CPA beyond the age of three, according to the definition of the American Psychological Association [32], is required. To be diagnosed with PTSD, patients must meet 1 B-criterion, 2 C-criteria, and 2 D-criteria in the Clinician Administered PTSD Scale for Children and Adolescents (CAPS-CA [33]). A stable psychopharmacological medication is necessary at study entry, i.e., in the last 3 weeks there was either no or a constant psychopharmacological medication. Moreover, living in safe conditions, a sufficient knowledge of German language, as well as an informed consent from the parents/legal guardians (if under 18) and the participant is compulsory.

Exclusion criteria are:

• Acute suicidality within the last 6 months

• Life threatening self-harming behavior within the last 6 months

• Substance-related or organic mental disorder

• Pervasive developmental disorder

• Acute or lifetime diagnosis of a psychotic disorder according to the Diagnostic and Statistical Manual of Mental Disorders, Fourth Edition (DSM-IV-TR [34])

• Acute or lifetime diagnosis of a bipolar disorder according to DSM-IV-TR

• Current diagnosis of substance dependence according to DSM-IV-TR (abstinence <6 months)

• Mental retardation (IQ ≤75)

• Simultaneous psychological or psychiatric treatment

### Planned interventions

Patients are enrolled either to TAU or D-CPT. Patients in TAU will be advised to look for treatment with other therapists in the respective areas. A detailed instruction to find a psychotherapist via internet will be given to the client by the coordinator of the respective study center. TAU patients will be monitored at the corresponding measurement points planned for D-CPT. After follow-up 1, patients can be enrolled into D-CPT if they wish to do so.

D-CPT is organized into four phases [25]. The treatment begins with a commitment phase comprising 5 sessions in 4 weeks. The aim of this phase is to build a therapeutic alliance and to increase and test the adolescents’ motivation for treatment. Safety plans are developed and anti-suicide contracts are signed. In phase 2, patients learn to tolerate and control intensive trauma-related emotions without acting in a dysfunctional way. For this reason, an emotion regulation training based on DBT-PTSD [27] is applied with 6 sessions in 4 weeks. Phase 3 comprises 15 sessions of CPT, according to Resick et al. [24], administered in high frequency (within 4 weeks); this is the central part of D-CPT. Dysfunctional beliefs related to the traumatic experiences are identified and modified by cognitive restructuring. In the last phase of treatment, developmental tasks specific to adolescence are introduced in 4 sessions during 4 weeks (one weekly session). The goal of this final therapy phase is to minimize the risk of future victimization and/or to prevent the choice of abusive partners. Moreover, the last treatment sessions focus on supporting the patient to complete education and to get an adequate vocational training. In sum, D-CPT comprises 30 sessions with 6 optional sessions for crisis intervention or communication with care givers or other institutions. Table 1 summarizes the treatment design and content. Adherence to D-CPT will be ensured by manualization, continuous local as well as central supervision, and ratings of therapeutic adherence and competence of random samples of videotaped sessions. Therapists are trained within one 4-day and one 2-day workshop. After attending the first workshop, every therapist treats at least one pilot case.

**Table 1 T1:** Overview of D-CPT

**Week**	**Sessions**	**Phase**	**Details**
1–4	5	Commitment	Therapy contract, emergency plan
			Lifeline
			Therapy goals
5–8	6	Emotion-regulation	Monitoring and identifying dysfunctional behavior and its long-term consequences
			Using distress tolerance skills
			Education about emotions
9–12	15	Intensive CPT	PTSD symptoms and psychological processes
			Identifying maladaptive beliefs (“stuck points”)
			Remembering the traumatic event through written accounts
			Challenging stuck points
			Focusing on special themes including safety, trust, control, esteem, and intimacy
13–16	4	Developmental tasks	Education about potentially abusive partners
			Education-focused help
			Inclusion of social network
			Review

### Outcome measurements

#### ***Primary outcome***

Severity of PTSD is measured at each assessment point using the CAPS-CA [33] (in German [35]). The CAPS-CA is a structured clinical interview which rates frequency and intensity of PTSD symptoms on a scale ranging from 0 (never) to 4 (daily or almost daily) and from 0 (none) to 4 (extreme), respectively. According to the German interview guidelines [35], a symptom is recorded as present if both frequency and intensity are at least rated with 1.

### Secondary outcome

A self-rating of PTSD symptoms is obtained weekly within therapy and at every assessment point using the University of California Los Angeles PTSD Reaction Index (UCLA [36], in German [37]).

At pre- and post-treatment as well as at follow-up 1 and 2 assessments, psychiatric comorbidity is measured with the Structured Clinical Interview for DSM Disorders (SCID [38,39], in German [40]), further important parts of the Diagnostic Interview for Mental Disorders in Childhood and Adolescence (Kinder-DIPS [41]), and the nicotine section of the Expert System for Diagnosing Mental Disorders (DIA-X [42]).

Moreover, patients are asked to complete a wide range of questionnaires measuring comorbidity and related problems at every assessment before and after treatment. Among these are:

• Trauma Symptom Checklist for Children (TSCC [43], in German [44])

• Beck Depression Inventory (BDI-II [45], in German [46])

• Adolescent Dissociative Experiences Scale (A-DES [47], in German [48])

• Borderline Symptom List 23 (BSL-23 [49])

• Youth Self-Report (YSR [50], in German [51])

• Modified version of the Client Sociodemographic and Service Receipt Inventory (CSSRI [52], in German [53])

• EuroQol 5 Dimensions (EQ-5D [54], in German [55])

Besides, saliva samples are collected for high-throughput epigenetic profiling and psychophysiological parameters are assessed by EEG – each at baseline and follow-up 1.

### Additional measures

Participants are tested with the Culture-Fair Intelligence Test (CFT-20-R [56]), which ensures that patients meet the cognitive requirements for treatment.

Detailed information about abuse are obtained by the Childhood Trauma Questionnaire (CTQ [57], in German [58]) and the Interview for Traumatic Events in Childhood (ITEC [59]). The ITEC is a retrospective, semi-structured interview for childhood maltreatment that provides dimensional scores for the severity of sexual, physical, and emotional abuse as well as emotional and physical neglect.

For the examination of mediators and moderators, like therapeutic alliance, maladaptive beliefs, and mental images, the Helping Alliance Questionnaire [60] (in German [61]), the Post-traumatic Maladaptive Beliefs Scale for Youth (PMBSY; [name], [name], [name], personal communication, 2012), and an instrument for the measurement of mental images (FVB; [name], [name], [name], [name], personal communication, 2012) are used. Emotion regulation is assessed using the Affective Style Questionnaire (ASQ [62], in German [63]) and attachment is studied by the Experiences in Close Relationships – Revised Questionnaire (ECR-R [64], in German [65]). Therapeutic adherence and competence are rated on the basis of randomly drawn videographies of treatment sessions by independent raters using two newly developed rating scales, the D-CPT Adherence Scale [66] and the Cognitive Therapy Competence Scale for D-CPT [66].

### Procedure

Patients will be sent by private practitioners, hospitals, school psychologists, and children’ services as well as child and adolescent mental health services. Homepages, newspaper reports, and leaflets in schools will support individual referrals. In a first interview, patients are screened for inclusion and exclusion criteria. If suitable, patients are informed about study conditions and asked to give informed consent. When this requirement is met, pre-diagnostic procedures comprising SCID, Kinder-DIPS, DIA-X, CAPS-CA, ITEC, CFT-20-R, several questionnaires (YSR, CSSRI, EQ-5D, ECR-R, ASQ, BDI-II, A-DES, BSL-23, CTQ, UCLA, TSCC, PMBSY, FVB), saliva sampling, and an EEG session are carried out. Patients are randomized to either TAU or D-CPT subsequently. After emotion-regulation training, patients in D-CPT are invited to complete process measures including the CAPS-CA and UCLA. For patients in TAU, this measurement is arranged around 8 weeks after randomization. After the end of treatment, post-diagnosis (directly after treatment), follow-up 1 (3 months after end of treatment), and follow-up 2 (6 months after end of treatment) measurements take place. These involve the SCID, Kinder-DIPS, DIA-X, CAPS-CA, and several questionnaires (YSR, CSSRI, EQ-5D, ECR-R, ASQ, BDI-II, A-DES, BSL-23, UCLA, TSCC, PMBSY, FVB) at each assessment point, as well as saliva collection and EEG at follow-up 1. These assessments are conducted by independent and trained interviewers who are blind to the treatment condition. Figure 2 shows the flow diagram of participant recruitment according to CONSORT [67].

**Figure 2 F2:**
[figure not shown]
**CONSORT flow diagram.** D-CPT, Developmentally adapted cognitive processing therapy; TAU, Treatment as usual.

### Sample size calculation

A type I error of 0.05 and a statistical power of 0.8 were used for sample size calculations. As there exists no effect size estimation for TAU in Germany, we suggest an effect size of d = 0.3. Based on the data reported by Harvey and Taylor [16], an effect size of d = 0.9 was assumed for D-CPT. Thus, two groups of n = 45 patients are required for the trial. No adjustment for drop-out is necessary as last observation carried forward substitution of the major study endpoint will be performed during the intention-to-treat analysis.

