### Statistical analysis

To test the hypothesis that D-CPT is superior to TAU, a confirmatory analysis of the study will be calculated as a *t*-test of post-treatment scores of the CAPS-CA. The critical value of alpha will be set to 0.05. Additional analyses focusing on secondary study endpoints or on generating hypotheses for subsequent studies will be performed on an exploratory basis using up-to-date sophisticated statistical models.

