## Discussion

Although the severe psychopathological consequences of sexual and/or physical abuse are known, only few studies report on the results of trauma focused psychotherapy for adolescents [19-23]. Consequently, chances were hitherto missed to administer effective treatments in early life to prevent the development of severe comorbidity or re-victimization. Reasons for the lack of studies are manifold, and might be due to difficulties in psychological assessments differing for adolescents and young adults, as well as to legal issues around different licensing procedures for therapists treating children and adolescents and those treating adult patients. Moreover, the lack of studies might be related to the characteristics of adolescents, whose motivational instability, rapid and intensive mood changes, and disentanglement from family structures have the potential to impede treatment participation and completion. The only published study on a similar methodological level needed 6 years of randomization to finally include 61 adolescent girls [23]. This highlights once more the specific problems in this age group. To bridge this knowledge gap by introducing a developmentally adapted CPT is the goal of the D-CPT network. The novelty of D-CPT is the adaption of the CPT procedure to the group of traumatized adolescents by increasing treatment intensity, integrating emotion-regulation-training, and finally by considering developmental tasks. The overall aim of the project is to evaluate this new therapy. Besides, the network aims to address several other heavily underexplored issues like variables influencing treatment outcome, epigenetics, health economics, and neurophysiological processing.

Taken together, the innovative character of our project is represented in i) a study sample of adolescents and young adults suffering from PTSD, ii) the developmentally adapted version of CPT (D-CPT) whose feasibility for youth within the German health system will be evaluated, and iii) measurement of the so far unknown effectiveness of TAU in Germany, which will be estimated.

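### Last observation carried forward does not remove the need for a drop-out allowance: it keeps 45 scores per arm but not the 0.6 SD difference on which 45 rests

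*Protocol article*

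**What the plan says.** The section Sample size calculation sets the error rates ("A type I error of 0.05 and a statistical power of 0.8 were used for sample size calculations") and two assumed effects. For TAU: "As there exists no effect size estimation for TAU in Germany, we suggest an effect size of d = 0.3". For the new therapy, "an effect size of d = 0.9 was assumed for D-CPT". It concludes: "Thus, two groups of n = 45 patients are required for the trial". It then rules out any allowance for loss: "No adjustment for drop-out is necessary as last observation carried forward substitution of the major study endpoint will be performed", within the intention-to-treat analysis.

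Under Statistical analysis, the confirmatory test is a t-test of post-treatment CAPS-CA scores, and "The critical value of alpha will be set to 0.05".

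Two other sections bear on this. Under Procedure, the only CAPS-CA between baseline and post-treatment is a process measure: "After emotion-regulation training, patients in D-CPT are invited to complete process measures including the CAPS-CA and UCLA". TAU patients have it about 8 weeks after randomisation. Table 1 places the intensive CPT phase in weeks 9 to 12, after that measure. The Discussion says of adolescents that their "motivational instability, rapid and intensive mood changes, and disentanglement from family structures have the potential to impede treatment participation and completion".

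**The concern.** A sample size for a t-test rests on two things: how many scores enter the test, and how far apart the arm means are relative to the SD. Last observation carried forward secures only the first. A patient without a post-treatment CAPS-CA enters with an older score, and this schedule offers only two: baseline, which carries none of the treatment difference, or week 8, which precedes the phase the article itself describes as central to D-CPT. Such scores pull the arm means together, and mixing improved with unimproved patients widens the spread.

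At stake is the power of the only confirmatory test. The method can also bias the estimate, with size and direction depending on how much each arm loses, how much each arm improves, and when patients leave.

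**Working it through.** **Inputs from the article.** Gains of 0.9 SD (D-CPT) and 0.3 SD (TAU), alpha 0.05, power 0.8, 45 per arm, t-test at post-treatment. Sidedness is not stated; the two-sided test is the one that gives 45 (one-sided gives 35).

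**Inputs assumed.** The article gives no loss rate, so 10, 20 and 30% are used. The share *f* of the gain already reached in the carried score is also unknown: *f* = 0 means baseline is carried, and *f* = 0.5 means half the gain is carried. SD is 1 in each arm, and loss is unrelated to outcome.

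**Step 1: the plan's own figure.** Difference 0.9 − 0.3 = 0.6 SD. From the noncentral t distribution, power is 79.5% with 44 per arm and 80.4% with 45. The stated 45 reproduces.

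**Step 2: equal loss *p* in both arms, 45 scores per arm after carrying forward.**
- Difference = 0.6 × (1 − *p* + *p f*)
- Arm variance = 1 + *p*(1 − *p*) × [(1 − *f*) × gain]²

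Example, *p* = 0.2 and *f* = 0: difference 0.6 × 0.8 = 0.48. Variances are 1 + 0.16 × 0.81 = 1.130 and 1 + 0.16 × 0.09 = 1.014, so the pooled SD is 1.035. Standardised difference 0.48 / 1.035 = 0.464; power 0.585.

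| Loss in each arm | Standardised difference, *f* = 0.5 | Power, *f* = 0.5 | Standardised difference, *f* = 0 | Power, *f* = 0 |
|---|---|---|---|---|
| 0% | 0.600 | 0.80 | 0.600 | 0.80 |
| 10% | 0.567 | 0.76 | 0.529 | 0.70 |
| 20% | 0.535 | 0.71 | 0.464 | 0.59 |
| 30% | 0.504 | 0.66 | 0.401 | 0.47 |

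Simulation (20,000 runs) agrees: 0.71 and 0.59 at 20%, 0.66 and 0.47 at 30%. For comparison, an unadjusted t-test on the 36 observed patients per arm at 20% loss has power 0.71. Carrying forward therefore does no better than losing those patients, and does worse if the carried score is baseline.

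**Step 3: unequal loss, planned gains, *f* = 0.**
- D-CPT 30%, TAU 10%: 0.7 × 0.9 − 0.9 × 0.3 = 0.36 SD, power 0.37.
- D-CPT 10%, TAU 30%: 0.9 × 0.9 − 0.7 × 0.3 = 0.60 SD, power 0.79.

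**Step 4: no true difference, D-CPT 10% and TAU 30% loss, *f* = 0.** The false difference is (0.9 − 0.7) × the common gain.
- Gain 0.3 (the planned TAU figure): 0.06 SD, type I error 5.9% (5.2% with *f* = 0.5).
- Gain 0.6: 0.12 SD, 8.5%.
- Gain 0.9: 0.18 SD, 12.5%.
- Equal loss (20% in each arm), any of these gains: 5.0%.

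**Step 5: what baseline adjustment could recover.** The article gives no baseline-to-post correlation *r*, so it is assumed. Adjusting observed scores for baseline reduces the SD by the factor √(1 − *r*²). At 20% loss at random, simulated power is about 0.74 at *r* = 0.3 and 0.82 at *r* = 0.5. Last observation carried forward with the same adjustment at *r* = 0.5 and baseline carried gives about 0.76.

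**The case against.** The loss rates are assumed. The Discussion speaks of taking part in and finishing treatment, whereas only a missing post-treatment interview triggers substitution; a patient who stops therapy may still be assessed. If almost nobody misses that interview, the stated power is nearly right. This stands, and it is why the figures are a range. It does not rescue the sentence, which claims no allowance is needed whatever the loss: even 5% equal loss gives 0.75 to 0.78.

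The baseline-carried figures are also the low end, because a week-8 CAPS-CA is scheduled in both arms. That stands too. How much of the gain is present at week 8 is unknown, so neither end of the range should be read as the expected value.

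The assumed effects might already include drop-outs. The article does not say so, and the reason it gives is the substitution method.

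Four stronger readings go beyond the documents:
- A reader might infer that the sample size was miscalculated. It was not; 80.4% reproduces with complete data.
- A reader might infer that the method creates a D-CPT benefit whenever TAU loses more patients. With the planned gains and 10% against 30% loss, the difference is exactly the planned 0.60.
- A reader might infer a type I error of 8.5 to 12.5%. That needs unequal loss, baseline carried forward, and both arms improving by 0.6 to 0.9 SD, which is two to three times the planned TAU gain.
- A reader might infer that replacing the method alone lifts power from 0.59 to 0.82 at 20% loss. Much of that contrast comes from baseline adjustment at an assumed correlation of 0.5.

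**Conclusion.** The concern holds for the stated inference. A power of 80.4% with 45 per arm requires the full 0.6 SD difference, and values carried forward from baseline or week 8 do not preserve it. At an assumed equal loss of 20%, power is 0.59 to 0.71; at 10% it is 0.70 to 0.76, and at 30% it is 0.47 to 0.66. These ranges rest on the assumed loss rate, on loss unrelated to outcome, and on zero to half of the gain being carried in both arms.

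The method is not reliably conservative either, but that part is smaller. Equal loss biases the difference towards zero and leaves type I error at 5%. With 10% against 30% loss and no true difference, type I error is about 5.9% at the planned TAU gain; larger inflation needs larger gains than planned for TAU. The case for change rests mainly on power.

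**What to change.** - Delete the sentence stating that no drop-out adjustment is needed.
- In the confirmatory analysis, replace last observation carried forward with a baseline-adjusted, likelihood-based mixed model on all randomised patients, or multiple imputation. Use the baseline, week-8, post-treatment and follow-up 1 CAPS-CA, with the contrast at post-treatment. All are already scheduled. Follow-up 2 is best left out, because TAU patients may enter D-CPT after follow-up 1.
- Keep last observation carried forward at most as a sensitivity analysis.
- Restate power at an assumed loss rate, for example 20%, with n kept at 90. Say openly that recovering 80% depends on the baseline-to-post correlation (about 0.74 at 0.3, 0.82 at 0.5).

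The cost is a change of wording, slightly more analysis work and a less favourable stated power; no extra patients or visits. Trial status reports 31 of 90 recruited, so the article's own figures suggest the change could be made well before the final data are in.

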### Statistical analysis

To test the hypothesis that D-CPT is superior to TAU, a confirmatory analysis of the study will be calculated as a *t*-test of post-treatment scores of the CAPS-CA. The critical value of alpha will be set to 0.05. Additional analyses focusing on secondary study endpoints or on generating hypotheses for subsequent studies will be performed on an exploratory basis using up-to-date sophisticated statistical models.

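### The confirmatory t-test and the sample size ignore possible therapist clustering in the D-CPT arm, so the standard error is too small if therapists differ, by an amount the protocol article does not let a reader fix

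*Protocol article*

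**What the plan says.** Under Statistical analysis, the article names one confirmatory test, a t-test on CAPS-CA after treatment. The sentence opens: "To test the hypothesis that D-CPT is superior to TAU, a confirmatory analysis of the study will be calculated as a". On the significance level it adds: "The critical value of alpha will be set to 0.05". No term for therapist or centre is mentioned, and more elaborate models are kept for secondary and exploratory work.

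Under Sample size calculation: "A type I error of 0.05 and a statistical power of 0.8 were used for sample size calculations". For TAU, "we suggest an effect size of d = 0.3"; for the new therapy, "an effect size of d = 0.9 was assumed for D-CPT". The result is 45 patients per group, with no ICC and no design effect.

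On delivery, the Study centers section says: "Treatment is offered in three university outpatient clinics". The Planned interventions section describes an individual therapy of 30 sessions, with trained and supervised therapists, and says: "After attending the first workshop, every therapist treats at least one pilot case". Under the same heading, TAU patients are told how to look for a therapist elsewhere. The number of D-CPT therapists and their trial caseloads are not given.

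**The concern.** Patients treated by the same therapist may have more similar outcomes than patients treated by different therapists. In this trial that grouping would arise in one arm. The D-CPT patients are shared among workshop-trained study therapists, whereas the TAU patients go to therapists they find themselves. This is a partially nested design. The article treats the therapist as relevant to outcome: under The current trial it lists therapist competence, adherence and working alliance among the variables that influence it, and competence and adherence are to be rated from session videos.

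A two-sample t-test sets the therapist variance to zero. If the true variance is positive and therapists treat more than one trial patient, the standard error of the D-CPT mean is understated. The confidence interval is then too narrow and the type I error exceeds the stated 5%, which makes a false claim of superiority for D-CPT more likely. The sample size rests on the same assumption and has almost no reserve.

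**Working it through.** **Inputs from the article.** 45 patients per arm; alpha 0.05; power 0.80; effect sizes 0.9 (D-CPT) and 0.3 (TAU), which imply a between-group d of 0.9 − 0.3 = 0.6.

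**Inputs that must be assumed.** The number of D-CPT therapists, k (6 to 15), and the therapist ICC (0.02 to 0.10). Equal caseloads, equal total variance in the two arms and no clustering in TAU are also assumed.

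**Step 1: reproduce the plan's figure.** For a two-sided t-test with independent patients, the noncentrality is 0.6 × √(45/2) = 2.846 on 88 degrees of freedom. This gives power 0.804, and 45 is the smallest size per arm that reaches 0.80. A one-sided test would need only 36. The stated 45 is therefore a two-sided calculation under independence.

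**Step 2: reserve.** With a design effect DE in the D-CPT arm only, the normal approximation gives

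n per arm = (DE + 1) × ((1.960 + 0.842)/0.6)² = (DE + 1) × 21.8.

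Setting n = 45 gives DE = 45/21.8 − 1 ≈ 1.06. Any larger design effect takes power below 0.80.

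**Step 3: size of the effect.** With m = 45/k patients per therapist:

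- DE = 1 + (m − 1) × ICC
- true SE / t-test SE = √((DE + 1)/2)
- power with the correct SE: the noncentrality 2.846 divided by that ratio, keeping 88 degrees of freedom

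Example, k = 6 and ICC 0.10: m = 7.5; DE = 1 + 6.5 × 0.10 = 1.65; ratio = √(2.65/2) = 1.151; noncentrality = 2.846/1.151 = 2.47; power 0.69.

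The type I error and rejection rate of the planned t-test were simulated, with at least 20,000 trials per case.

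| Therapists | ICC | DE | SE ratio | t-test type I error | Power, correct SE | Rejection rate of planned t-test at d = 0.6 |
|---|---|---|---|---|---|---|
| 15 | 0.02 | 1.04 | 1.010 | 0.052 | 0.80 | 0.80 |
| 15 | 0.05 | 1.10 | 1.025 | 0.056 | 0.78 | 0.80 |
| 9 | 0.05 | 1.20 | 1.049 | 0.06 | 0.77 | 0.79 |
| 9 | 0.10 | 1.40 | 1.095 | 0.073 | 0.73 | 0.78 |
| 6 | 0.10 | 1.65 | 1.151 | 0.089 | 0.69 | 0.77 |

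Outside this range, 22 therapists with ICC 0.02 give an SE ratio of 1.005 and a type I error of 0.050, which is negligible. Three therapists (one per clinic) with ICC 0.10 give 1.30 and 0.13. With an ICC of zero nothing changes.

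The last two columns describe different tests. The planned t-test keeps most of its rejection rate because it uses the understated standard error, and the cost appears in the type I error column. The corrected-SE column keeps 88 degrees of freedom. Small-sample degrees of freedom would lower it further when therapists are few.

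**The case against.** The strongest reply is that the key facts are not in the article. A reader might infer that a handful of therapists treated all the D-CPT patients and that the standard error is therefore certainly too small. The documents do not support that. They name three clinics but no therapist count or caseload, and the sentence on pilot cases says nothing about trial patients per therapist. A positive ICC is also an assumption. Rating competence and adherence shows that the authors think therapists may matter, not that they differ materially. The manual, the local and central supervision and the adherence ratings are meant to reduce such differences. It is also not excluded that some TAU patients share a therapist. All of this stands, so the point has to be conditional.

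A second tempting reading is that the planned test has power of only 0.69. That is wrong: 0.69 belongs to a test with the corrected standard error under the least favourable assumptions in the table, and the planned t-test would reject in about 0.77 of trials there.

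A statistical analysis plan may exist that is not shown. It could repair the test only by departing from the article, which names the t-test as the confirmatory analysis. The exploratory models do not change that test.

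**Conclusion.** The point holds in conditional form. The confirmatory test and the sample size both assume independence, and the way D-CPT is delivered makes that doubtful in one arm. Whenever the therapist ICC is positive and therapists treat more than one trial patient, the t-test's type I error is above 5%. Over the assumed range the excess runs from trivial (0.052) to material (0.089). The article gives no figure that would show which end applies. A proportionate conclusion is that the analysis should be changed, not that the result would be invalid.

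**What to change.** Record the therapist ID for each D-CPT patient. Make the confirmatory analysis of post-treatment CAPS-CA a model with a therapist random effect in the D-CPT arm only, arm-specific residual variance, and Satterthwaite or Kenward–Roger degrees of freedom. Report the number of therapists and the estimated ICC. Fix this before outcomes are analysed; when the article was written, 31 of 90 patients had been recruited.

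As a separate gain in precision, adjust for the baseline CAPS-CA, which is already collected. If adjustment scales all variance by 1 − ρ², where ρ is the baseline to post-treatment correlation (not given in the article), the SE increase is offset when 1 − ρ² = 2/(DE + 1). For 9 therapists and ICC 0.05 that is 2/2.20 = 0.91, so ρ ≈ 0.30. For 6 therapists and ICC 0.10 it is 2/2.65 = 0.755, so ρ ≈ 0.50. The loss of degrees of freedom comes on top.

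**Cost.** A change of analysis wording and one variable that the clinics already know; no new patients or assessments. The interval becomes somewhat wider, by up to about 15% under the assumptions above before the change in degrees of freedom. With few therapists the therapist variance will be imprecisely estimated.
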